# Research protocol local ingredients-based supplementary food as an alternative to corn-soya blends plus for treating moderate acute malnutrition among children aged 6 to 59 months: a randomized controlled non-inferiority trial in Wolaita

**DOI:** 10.1186/s12889-019-8031-3

**Published:** 2019-12-16

**Keywords:** Moderate acute malnutrition, Local ingredients-based supplement, Corn-soya blend plus, Randomized controlled non-inferiority trial, Effectiveness

## Abstract

**Background:**

In Ethiopia, 12.5% of children below 5 years are wasted, and 9.7% are moderately wasted. The present strategy for the management of moderate acute malnutrition (MAM) is a supplementary feeding program; however, this is only provided to chronically food-insecure areas. This randomized controlled non-inferiority trial examines if Local ingredients-based supplement (LIBS) is as effective as corn-soya blends plus (CSB+) in treating moderate acute malnutrition among children aged 6–59 months.

**Methods:**

A randomized controlled non-inferiority trial will be conducted with moderately wasted children aged 6 to 59 months in Wolaita, Ethiopia. The calculated sample size is 324 (i.e. with 162 children in each of two arms, to be assigned by randomization). The daily ration will be: 100 g of LIBS plus 25.2 g of sugar with 8 ml oil in the intervention group, and 150 g of CSB+ with 16 ml of oil in the control group. These interventions will be provided for a maximum period of 12 weeks, with follow-up performed on a weekly basis. Data analysis will be done using SPSS and STATA software. Both intention-to-treat and per protocol analyses will be done. Hazard ratio and Kaplan-Meier (log rank) curves of survival analysis will be done to predict the probability of recovery rate. Logistic regression will be used to test for interactions between independent and dependent variables. Analysis of variances, t-tests, fisher’s exact test and chi-square tests will be used to assess baseline characteristics.

**Conclusions:**

This paper will introduce to the existing research locally available nutritious foods which have the potential to enhance recovery from moderate acute malnutrition and to reduce the burden of malnutrition. The perceptions of mothers on feeding children with local ingredient-based supplementary food to assist recovery from moderate acute malnutrition will be the focus of in a qualitative study to follow; this will provide a further contribution in an evolving area of research.

**Trial registration:**

Pan-African Clinical Trial Registration number: PACTR201809662822990, retrospectively registered on 11/09/2018.

## Background

Worldwide, acute malnutrition is a major contributor to deaths and disabilities in children, affecting about 51.5 million children below 5 years of age [1, 2]. Chronic food insecurity, poverty, poor feeding practice, limited household food availability and infections are considered possible reasons for developing acute malnutrition [3]. Acute malnutrition is associated with at least 12.6% child mortality, occurring among children aged below 5 years [2].

The Ethiopian Demographic and Health Survey of 2011 showed that about 10% of children aged below 5 years had acute malnutrition, and among these, 70% had MAM, defined by weight-for-height z-score (WHZ) between − 3 to − 2 Standard Deviations and/or mid-upper arm circumference (MUAC) of between ≥11.5 cm and < 12.5 cm, without bilateral pitting edema [4, 5]. Most malnutrition-related deaths occur in mildly or moderately malnourished children. In low- and middle-income countries, acute malnutrition is associated with about one in six deaths. Of these, 10.2% are due to MAM [6]. The death risk among moderately malnourished children is three-fold compared with that of non-malnourished children [1].

Children with MAM are susceptible to develop severe acute malnutrition (SAM) if they are not managed adequately. It is known that SAM has a high contribution to the global morbidity and mortality of young children. Therefore, children with MAM need to be treated with adequate nutrient-dense foods to prevent progressing to the life-threatening condition [2, 4].

In Ethiopia, the existing strategy for the management of MAM is a supplementary feeding program; however, this is restricted to districts where chronic food insecurity is present. In the areas not determined to be chronically food insecure, there are no food supplementation programs for MAM children. In these districts, the strategy to manage MAM children includes vitamin A supplementation, deworming and dietary counseling provided to the families [2]. The dietary counseling is provided to the families in these districts on the understanding that they have access to all foods required for child feeding, but lack knowledge on how best to use them [7].

In a study done in South-Western Ethiopia, without having a targeted nutrition-specific supplement to address MAM, only half of children aged 6 to 59 months recovered from MAM within 28 weeks of follow-up, with health and dietary counseling services alone. They were provided such services according to the national policy, but the recovery rate remained unsatisfactory. Even though these districts are named as food-secure areas, there are food-insecure households with acute moderately malnourished children suffering from high rates of deterioration and no improvement with the existing management. This is because household food insecurity is not determined by the food security level of districts [2].

Clinical strategies on the management of SAM have been present for many years. The implementation of these strategies has yielded positive outcomes. However, consistent study on the management of MAM is lagging behind, and much of the data is published on SAM, even if MAM is more prevalent and a gateway to developing SAM [8–10].

Children with MAM living in food-insecure areas are getting corn soya blend plus (CSB+) as a conventional supplement. Generally, CSB+ is given as a treatment to MAM children in developing countries since it has a good nutritional value for limited cost. However, there has been considerable argument in the international nutrition community concerning the nutritional suitability and competence for the treatment of MAM. CSB+ is believed by some to be a poor choice as a treatment since it does not contain important nutrients in acceptable amounts; it contains comparatively high amounts of anti-nutrient and fiber. In addition, it has a generally low fat level, and thus needs vegetable oil in order to provide the essential fatty acids and energy [11]. According to the report of different literature, the recovery rate after 8 to 16 weeks follow-up with CSB+ treatment is within the range of 67 to 76.8% [12–14].

The nutritional management of MAM have to normally be initiated on optimum usage of Local ingredient-based nutritious food [4]. Local ingredients based supplementary food are available, accessible, can be formulated at the household level and contain adequate amounts of the required nutrients [13].

In this paper, the new supplementary food referred to as Local ingredients based supplement (LIBS) made of locally available ingredients such as pumpkin seed, peanut, amaranth grain, flaxseed, and emmer wheat. Their portion designed to have the required amount of nutrients for the management of MAM among children aged 6 to 59 months.

In Ethiopia, Pumpkin cultivates widely and it is a seasonal crop that has been used for human food. Traditionally, consumers in Ethiopia using sun dried pumpkin fruit targeting at extended period storage for use during off season as part of food security plan [15]. Pumpkin is usually grows both in maize fields and vegetable gardens as well as in other more intensive agricultural systems [16]. Amaranth grain is a widely growing seed in Ethiopia [17]. It is mainly cultivated by people living in Southern Ethiopia as intercropped with sorghum and maize [18]. Emmer wheat is grown-up in marginal land in almost all districts of Ethiopia in both ‘Meher’ (June to September) and ‘Belg’(March to May) time of year [19]. Oilseed crops like peanut and flaxseed are widely cultivated in Ethiopia and consistently found in the local markets.

To confirm timely treatment of MAM and resolve the restricted distribution of supplement among beneficiaries, LIBS need to be developed. Besides this, adequate research has not been conducted in Ethiopia on Local ingredient-based supplementary food, although it has the potential to contribute to treating MAM. The information drawn from this study will be shared with the public, policymakers and academics, as locally available nutritious foods have the potential to enhance recovery from MAM and reduce the burden of malnutrition.

### Aim of the study

The objective of this study is to evaluate if LIBS is as effective as standard corn-soya blend plus in treating MAM among children aged 6 to 59 months.

### Hypothesis

In MAM children aged 6 to 59 months, intervention with LIBS will, within 12 weeks (with a 7% margin of non-inferiority), will not have an inferior recovery rate as children with MAM receiving CSB+.

## Methods

### Study design

A randomized, controlled, non-inferiority trial will be carried out to evaluate the efficacy of LIBS (the intervention), compared with conventional treatment which is CSB+ (a control), in treating MAM.

### Setting

This study will be conducted in Damot Pulassa district located in Wolaita zone. Like other districts of Wolaita, this district has the highest population densities of more than 700 persons per square kilometer [20]. The district characterized by having a fragmented farm and land ownership. The disparity between land and population balance has by far persisted the main contributing factor for the occurrence of endemic food insecurity [21]. Damot Pulassa district is classified as a maize and root crop livelihood zone because such crops are the main ones produced in the area. The district is serving by five health centers and 23 health posts. These health posts are led by health extension workers and deliver nutrition-linked services like nutrition education, screening for nutritional status of young children and nutritional management of the malnourished ones. The district was selected based on a consideration of the high level of food insecurity, high level of child malnutrition, good geographical location and access to transportation.

### Study population

The study population will be children with MAM, MUAC of ≥11.5 cm and < 12.5 cm without bilateral edema and/or with weight-for-height z-scores between − 3 to − 2 Standard Deviations [4, 5]. Mothers or caregivers of selected children will be the respondents.

### Inclusion criteria

All children 6 to 59 months of age identified as MAM (MUAC of ≥11.5 cm and < 12.5 cm) [5].

### Exclusion criteria

Children with SAM based on WHO 2009 child growth standards and/or children with bilateral pitting edema [22].Children with any illness or other medical complications that prevent them from safely consuming supplementary food.Children already participating in other interventions.

### Sample size calculation

The proportion of children who recover from MAM in an area where there is a supplementary feeding program (CSB+) is about 67% [12]. The sample size assumes that the expected percentage response in an experimental group is 60% and in a control group is 67%, with the non-inferiority criterion set to be an absolute value of 7%. To achieve 80% power to demonstrate non-inferiority, it is estimated that 162 subjects per group would be required, including a 10% withdrawal rate. This leads to a total required sample size of 324 subjects. The anticipated 10% dropout rate was used based on the observed dropout rate reported in two studies [12, 13]. For this sample size calculation, the PharmaSchool sample size calculator for non-inferiority trials was used.

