### Data analysis

All data collection sheets will be controlled by the field supervisors for completeness. EpiData version 3.1 will be used for all data entry. Two data clerks will enter data simultaneously to ensure data quality. Continuous data quality evaluation will be made through automatic consistency checks. Statistical significance is set at 5% for all analyses. Statistical analysis will be done using SPSS and STATA software for survival and hazard ratio. The probability of recovery rate will be predicted in Kaplan-Meier (log rank) curves of survival analysis. T-tests, analysis of variance (ANOVAs) and chi-square tests will be used to assess baseline characteristics. In accordance with recommendations for analyzing and reporting equivalence and non-inferiority trials, both intention-to-treat (ITT) and per protocol (PP) analyses will be done, and the 95% CI will be used to infer whichever variances are significant [24]. The ITT analyses will include all children enrolled in the study whereas the PP analyses will exclude children who lost to follow-up, refused and transferred out of the management programme but include children discharged as cured, died or non-cured.

Logistic regression will be used to test for interactions between the recovery rate and other variables. Mean recovery time and median recovery time, mean differences of MUAC and mean difference between WHZ scores will be computed to describe the magnitude of the difference between the two groups.

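### The assumed 60% vs 67% recovery lies exactly on the 7-point non-inferiority limit, so power is 2.5–5% rather than 80%, and only about 25% (35% at one-sided 5%) if the foods are equal

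*Protocol article*

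**What the plan says.** The Sample size calculation section takes 67% as the recovery proportion under CSB+ from an earlier study. It then sets the planning values: "The sample size assumes that the expected percentage response in an experimental group is 60% and in a control group is 67" per cent, "with the non-inferiority criterion set to be an absolute value of 7" per cent. From these it concludes: "To achieve 80% power to demonstrate non-inferiority, it is estimated that 162 subjects per group would be required, including a 10% withdrawal rate". The total is 324. A named sample size calculator is cited, but its entries, formula and alpha are not given.

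The Hypothesis section repeats the margin ("with a 7% margin of non-inferiority") for recovery within 12 weeks, so a higher proportion is better and LIBS passes if it is less than 7 points worse.

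The Data analysis section sets significance at 5%, plans both intention-to-treat and per-protocol analyses, and says that "the 95% CI will be used to infer whichever variances are significant".

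**The concern.** A non-inferiority trial has power only if the assumed true difference lies on the favourable side of the margin. Here the assumed difference (60 − 67 = −7 points) is the non-inferiority limit itself (−7 points). The inputs, the margin, the power and the sample size stand together in one paragraph and cannot all be true.

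This is the only justification given for the size of the trial and for its primary conclusion. A reader who trusts 80% power will take a failure to show non-inferiority as evidence that the local food is worse. If the real power is far lower, such a failure says very little, and the article's Discussion intends the result to guide policymakers.

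**Working it through.** **Inputs.** From Sample size calculation: pT = 0.60 (LIBS), pC = 0.67 (CSB+), margin M = 0.07, power 80%, withdrawal 10%, 162 per arm. Evaluable per arm: 162 × 0.9 = 145.8, about 146. From Data analysis: 5% significance and a 95% CI. If two-sided, the usual reading, that interval is a one-sided 2.5% test. Both 2.5% and 5% one-sided are shown.

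**Formula.** n per arm = (zα + zβ)² × [pT(1 − pT) + pC(1 − pC)] / [M − (pC − pT)]²

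**1. The stated inputs.** The denominator is [0.07 − (0.67 − 0.60)]² = 0. No finite n exists at either alpha.

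**2. Where 162 can come from.** Take the 7-point difference in favour of LIBS, so that the distance to the margin is 0.07 + 0.07 = 0.14, and use one-sided 5%:

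- Variance term: 0.67 × 0.33 + 0.60 × 0.40 = 0.2211 + 0.2400 = 0.4611
- n = (1.6449 + 0.8416)² × 0.4611 / 0.14² = 6.183 × 0.4611 / 0.0196 = 145.4
- With withdrawal: 145.4 / 0.9 = 161.6, so 162

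A pooled-variance version at the same 14-point distance and alpha gives 146.2; rounded up to 147 and multiplied by 1.1, it is 161.7, again 162. The other routes tried do not come near 162. Before withdrawal they give:

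| Route | one-sided 2.5% | one-sided 5% |
|---|---|---|
| Equal rates of 67% | 709 | 558 |
| Equal rates of 60% | 769 | 606 |
| Superiority, 60% vs 67% | 742 | 584 |
| 14-point distance, LIBS better | 185 | 146 |

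**3. Power of the planned trial.** Power = Φ([M − (pC − pT)] / SE − zα), with SE = √{[pT(1 − pT) + pC(1 − pC)] / n}. At n = 146, SE = √(0.4611/146) = 0.0562 for 60/67 in either direction, and √(0.4422/146) = 0.0550 for 67/67. Examples under the 95% CI:

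- 60 vs 67: Φ(0/0.0562 − 1.96) = 2.5%
- 67 vs 67: Φ(0.07/0.0550 − 1.96) = Φ(−0.69) = 24.6%
- LIBS 67 vs CSB+ 60: Φ(0.14/0.0562 − 1.96) = Φ(0.53) = 70.2%

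| True recovery, LIBS vs CSB+ | 146/arm, 95% CI | 146/arm, one-sided 5% | 162/arm, 95% CI | 162/arm, one-sided 5% |
|---|---|---|---|---|
| 60% vs 67% (as stated) | 2.5% | 5.0% | 2.5% | 5.0% |
| 67% vs 67% | 24.6% | 35.5% | 26.8% | 38.0% |
| 67% vs 60% | 70.2% | 80.1% | 74.7% | 83.6% |

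Exact binomial enumeration of the Wald-limit rule agrees. With 146 per arm it gives 2.6% and 4.9% for the first row and 25.0% and 35.4% for the second.

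**4. Precision.** At 67% in both arms with 146 each, the 95% CI half-width is 1.96 × 0.0550 = 0.108, or 10.8 points. To keep the lower limit above −7, LIBS must be observed 10.8 − 7 = 3.8 points better than CSB+.

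**5. Size needed for 80% power at equality (67%).** (1.960 + 0.8416)² × 0.4422 / 0.07² gives 709 evaluable per arm; 709 / 0.9 gives 788 enrolled. At one-sided 5% the figures are 558 and 620.

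**The case against.** The most charitable reading is that 60% is not an expected rate but the lowest acceptable one (67% minus 7), with the foods assumed equal. The text calls it an expected response, but even this reading does not rescue the figure: equality needs 558 to 709 evaluable per arm, not 146.

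Three narrower objections have some force.

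- The cause is inferred. The calculator's entries are not shown, and the match to 162 depends on rounding: taking 146 first gives 146 / 0.9 = 162.2, which rounds up to 163. It is fair to say that 162 is reproduced by a difference in favour of LIBS at one-sided 5%, and no more. The defect does not depend on how the number arose.
- The article does not say whether the 95% CI is one- or two-sided. The 25% and 70% powers, the 10.8-point half-width and the 3.8-point requirement all assume the usual two-sided interval.
- The intention-to-treat set includes all enrolled children, so 162 per arm may apply there. Across both analysis sets and both alphas, power at equality is 25% to 38%.

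None of these brings power near 80% under the stated rates or under equality.

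**Conclusion.** The concern holds. Under the protocol's own rates and margin, power equals alpha, 2.5% or 5%, whatever the sample size. The stated 80% is impossible, and no other section repairs it. If the foods are equal at 67%, power is about 25% with 146 evaluable per arm and a two-sided 95% CI, and at most 38% under the most favourable combination of alpha and analysis set. Power of 80% with 146 evaluable per arm requires LIBS to be truly 7 points better and a one-sided 5% test; under the planned 95% CI, that same scenario gives about 70%. So there is also a mismatch between the alpha that reproduces 162 and the alpha implied by the analysis.

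The impossibility of the 80% claim needs no assumption beyond the stated figures. The power figures use the normal approximation for a difference in proportions, confirmed by exact enumeration for the stated and equal-rate scenarios. This must be corrected.

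**What to change.** Keep 324 children and correct the statement in Sample size calculation:

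- Delete the claim of 80% power under 60% vs 67%.
- Restate power for 146 evaluable per arm with a two-sided 95% CI: about 2.5% at 60% vs 67%, about 25% if both foods recover 67%, and about 70% only if LIBS is truly 7 points better.
- State the expected 95% CI half-width, about 11 points, beside the 7-point margin.
- Name one alpha, with its sidedness, and use it in both the sample size and the Data analysis sections.
- Add the reading rule in advance: non-inferiority is shown if the lower limit for LIBS minus CSB+ lies above −7 points; a lower limit below −7 is inconclusive unless the whole interval lies below −7.

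The cost is protocol wording and a much less favourable stated power; no extra children are needed. This makes the trial honest about what it can show but does not make it adequately powered. For scale, 80% power at equality with this margin would take 788 enrolled per arm (2 × 788 = 1,576 in total), or 620 per arm (1,240) at one-sided 5%, about four to five times the planned size.

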### Recruitment of study participants and randomization

Data collectors with health extension workers will visit all households with children aged 6 to 59 months. They will assess for eligibility by measuring the children’s MUAC. If the child has a MUAC of < 12.5, data collectors will register and send the caregiver with the child to the actual screening site, where MUAC will be re-measured and weight and height or length will be taken. Children aged 24 to 59 months will be measured for weight and height, and children aged 6 to 23 months will be measured for weight and length. In addition to the values of MUAC (i.e. 11.5 cm to 12.5 cm), we will use the z-scores of weight for height or weight for length for recruitment (i.e. weight-for-height z-scores: between − 3 to − 2 Standard Deviations). If the child is identified as moderately malnourished according to the MUAC and not according to the values of weight-for- height/length z-scores, we will recruit them with their MUAC values. The screening procedure will be conducted by trained data collectors and facilitated by health extension workers using both MUAC and WHZ. Edematous malnutrition will also be evaluated using bilateral pitting edema criterion. The screening process will be continued until the sample size is met.

Computer generated sequentially numbered randomization list that contained codes for children who meet enrolment criteria will be prepared by the research supervisor. These children will be randomized into intervention or control groups, using random allocation software. The allocation ratio will be 1:1 (Fig. 1).

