### Outcome variables

The primary outcome measure of this study will be recovery rate. ‘Recovered’ will be defined as when a child attains a MUAC ≥12.5 cm and WHZ scores ≥ − 2, without bipedal edema. The secondary outcomes are the mean recovery time and average weight gain. Children who developed SAM during the study and/or persisted as moderately malnourished at the end of the 3-month follow-up will be considered to have failed the management for MAM.

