### Participant timeline

Children aged 6 to 59 months will be assessed for MAM based on inclusion and exclusion criteria using MUAC and weight-for-height/length z-scores. The screening procedure will end within 3 weeks. Consenting of the eligible respondents (mothers of children aged 6 to 59 months) and randomization of the eligible subjects will take place 1 week after screening completed during which the subjects will be allocated into intervention and control groups, along with baseline data collection. Follow-up interviews with the anthropometric assessment will be done weekly and monthly basis after the allocation date and completed within 11 weeks. End-line data collection will take place 1 week after ending a follow-up interview (Fig. 2).

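### Baseline MUAC and WHZ are known before randomisation and probably predict recovery, but the article describes no arm comparison that uses them; the cost is modest precision, not bias

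*Protocol article*

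**What the plan says.** **Allocation.** Under Recruitment of study participants and randomization the article says: "These children will be randomized into intervention or control groups, using random allocation software. The allocation ratio will be 1:1". No stratum, block or minimisation factor is named. Children are grouped by neighbourhood only after allocation, to organise food distribution.

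**What is known at allocation.** Children go to a screening site "where MUAC will be re-measured and weight and height or length will be taken". Under Participant timeline, "The screening procedure will end within 3 weeks", and "randomization of the eligible subjects will take place 1 week after screening completed". MUAC and WHZ are therefore on record for the full cohort before any child is allocated.

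**Entry and exit.** Entry MUAC runs from 11.5 cm to below 12.5 cm. A child who is moderately malnourished by MUAC but "not according to the values of weight-for- height/length z-scores, we will recruit them with their MUAC values". Under Outcome variables, recovery "will be defined as when a child attains a MUAC ≥12.5 cm and WHZ scores" of at least -2, without oedema.

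**Analysis.** Under Data analysis: "T-tests, analysis of variance (ANOVAs) and chi-square tests will be used to assess baseline characteristics". The abstract adds Fisher's exact test for the same purpose. Logistic regression is planned to look at recovery in relation to other variables. Those variables are not named, and the article does not describe the regression as an adjusted comparison of the arms.

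**The concern.** With fixed exit thresholds, starting distance should matter. A child entering just under 12.5 cm with WHZ already above -2 has a small gap on one criterion. A child entering at 11.5 cm with WHZ close to -3 has to gain about 1 cm and nearly 1 z-score. Within one 12-week window these two children would be expected to recover at different rates.

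Baseline significance tests make no use of that information. Under randomisation their null hypothesis is true by construction, and they neither change the estimate nor narrow its interval. An estimate adjusted for baseline severity does narrow it. The interval here has to clear a 7-point margin, so precision obtainable from data already collected is worth having.

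**Working it through.** **1. The plan's own figure.** The article gives 162 per arm for 67% versus 60% recovery, a 7-point margin and 80% power, including 10% withdrawal. Taken as stated, the distance to the margin is 7 - 7 = 0, so no finite sample size exists. The figure appears only if the expected deficit is counted as an advantage, at one-sided 5%:

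(0.67×0.33 + 0.60×0.40) × (1.645 + 0.842)² / 0.14² = 145.4, and 145.4 / 0.9 = 161.6, i.e. 162.

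That is a separate problem. Below, 162 per arm is simply taken as given.

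**2. Interval width without baseline information.** With both arms at 67%: SE = √(2×0.67×0.33/162) = 0.0522. Half-width = 1.96 × 0.0522 = 10.2 points.

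**3. Effect of using baseline severity.** Let R² be the share of variance in recovery explained by baseline MUAC and WHZ. No document gives it, so it is assumed. The variance is multiplied by about (1 - R²) and the half-width by √(1 - R²). Power is for equal arms against the 7-point margin at one-sided 2.5%, which matches a two-sided 95% CI: Φ(0.07/SE - 1.96).

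| Assumed R² | Half-width (points) | Power |
|---|---|---|
| 0 | 10.2 | 26.8% |
| 0.03 | 10.24 × √0.97 = 10.1 | not computed |
| 0.05 | 10.0 | 27.9% |
| 0.10 | 9.7 | 29.2% |
| 0.20 | 9.2 | 32.2% |

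**4. Simulation check.** 4,000 trials per row, 162 per arm, 67% recovery, and a single standardised severity score standing in for MUAC and WHZ. Adjustment is by standardisation from a logistic model; stratification is by quartile of the score. Entries are the variance of the risk difference relative to simple randomisation without adjustment (Monte Carlo error about 0.02 to 0.03).

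| Odds ratio per SD | R² | Adjusted | Stratified | Both |
|---|---|---|---|---|
| 1.0 | 0 | 1.00 | 1.01 | 1.01 |
| 1.5 | 0.03 | 0.97 | 0.99 | 0.98 |
| 2.0 | 0.09 | 0.90 | 0.86 | 0.85 |
| 3.0 | 0.19 | 0.83 | 0.80 | 0.78 |

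The reduction is about 3% to 17% with adjustment alone and about 2% to 22% with both. Most of the gain comes from adjustment.

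**5. What chance imbalance can do.** For a severity stratum holding half the children, the between-arm difference in its share has SD √(2×0.5×0.5/162) = 5.6 points, with a 95% range of ±10.9 points. If that stratum changes recovery by an assumed 20 to 30 points, the risk difference moves by up to 0.109 × 20 = 2.2 to 0.109 × 30 = 3.3 points. The unadjusted interval already allows for this movement; adjustment removes it.

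**6. Limit of the remedy.** For 80% power with equal arms at 67% and one-sided 2.5%, 709 per arm are needed before dropout. With R² = 0.20 this becomes 709 × 0.8 = 567.2, i.e. 568, still far above 162.

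**The case against.** The strongest case against is that this rests partly on silence in a condensed article. The article does not say that randomisation is unstratified, and covariates for the primary comparison are often left to an analysis plan, which is not shown. That stands as a limit: an adjusted analysis may exist elsewhere. What remains is that the baseline significance tests are stated in both the abstract and Data analysis, and that the allocation method is described without strata.

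A reader might infer several stronger things that the documents do not support:

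- **That the comparison is biased.** It is not. Simple randomisation is valid, and the unadjusted interval already covers chance imbalance.
- **That baseline severity is only significance-tested.** The planned logistic regression may include baseline MUAC or WHZ. Its wording is too loose to tell, and it is not presented as an adjusted arm comparison.
- **That starting distance largely decides recovery.** No passage says how strongly it does. It follows from the outcome definition that some association is likely, and no more.
- **That adjustment is worth about a third more children.** A threshold model with a between-child SD of MUAC gain of 0.3 cm gives a variance ratio of 1.35. The same model gives 1.21 at 0.4 cm and 1.09 at 0.6 cm. In a similar model, an assumed baseline measurement error of 0.2 (cm and z) lowers the ratios to 1.22, 1.14 and 1.08. None of these SDs comes from the documents, so 1.35 is the top of an assumed range.
- **That stratification is essential.** On top of adjustment it moves the relative variance by 0.05 at most, close to simulation error. Without an analysis that uses the strata, it does not narrow the reported interval.

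**Conclusion.** The point holds as a loss of efficiency. Baseline MUAC and WHZ are available for every child before allocation and are likely to predict a threshold-based outcome, yet the article describes no arm comparison that uses them. Under an assumed R² of about 0.03 to 0.20, using them removes roughly 2% to 22% of the variance of the risk difference, or about 0.1 to 1.0 point of CI half-width at 162 per arm and 67% recovery. If the true prognostic strength is near zero, so is the gain.

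This is a worthwhile improvement at almost no cost, not a threat to validity. It should not be read as a remedy for the sample size: even at R² = 0.20, power with equal arms is 32.2%.

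**What to change.** 1. **Primary estimate.** Prespecify the recovery risk difference adjusted for baseline MUAC and WHZ as continuous covariates, with its 95% CI compared with the 7-point margin, in both the intention-to-treat and per-protocol analyses. Standardisation from a logistic model is one suitable method. It keeps the result on the absolute scale on which the margin is set, which an adjusted odds ratio would not.
2. **Baseline value.** Name the measurement that serves as baseline. The screening-site values certainly precede allocation and should be complete, since they are used to judge eligibility.
3. **Baseline table.** Replace the t-tests, ANOVA, chi-square and Fisher's exact tests of baseline characteristics with a descriptive table by arm.
4. **Allocation, only if not yet done.** Stratify the list by baseline MUAC and WHZ status and include the strata in the analysis. The registration is described as retrospective, so this step may no longer be open; the adjustment does not depend on it.

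The cost is a short addition to the analysis text and, if still possible, one setting in the allocation software. No extra children, visits or measurements are needed. The covariates must be fixed before outcomes are compared by arm.
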